## Abstract

**Background:**

The benefit-risk of statins in patients with lobar intracerebral hemorrhage (ICH) is under investigation in the StATins Use in intRacerebral hemorrhage patieNts (SATURN) trial. The relationship between statin use in ICH survivors, MRI markers of cerebral small vessel disease (CSVD), and outcomes such as recurrent ICH or major adverse cardiovascular or cerebrovascular events (MACCE) is unclear. The ancillary study, SATURN-MRI, intends to evaluate the interrelationship between statin use, the progression of MRI markers of CSVD, and cognitive and functional outcomes. Additionally, SATURN-MRI aims to assess whether baseline MRI markers of CSVD interact with statin continuation for the outcomes of recurrent ICH or MACCE in patients with lobar ICH.

**Methods:**

A target of 894 SATURN participants will undergo a baseline MRI within 7 days of randomization and a repeat MRI at the end of the 24-month follow-up period. Any SATURN subject without contraindication to MRI has the option to participate in SATURN MRI. MRIs will be reviewed by blinded central raters to assess for the presence and burden of markers of CSVD and their progression. The primary outcome is new cerebral microbleeds and/or sulci with cortical superficial siderosis identified on T2*-weighted (GRE, SWI or SWAN) images between baseline and end-study MRI. Additional outcomes include the progression of white matter hyperintensity and incidence of covert infarcts.

**Discussion:**

The results will provide insights about the interrelationship between the effects of statins, progression of MRI markers of CSVD, and functional and cognitive outcomes. They might lead to the validation of MRI markers as tools to assist with individualized decision-making regarding the effects of statins continuation/discontinuation in patients with lobar ICH.

**Trial registration:**

ClinicalTrials.gov NCT03936361. SATURN Trial was originally registered on May 1, 2019 and modified on February 28, 2022.

**Supplementary Information:**

The online version contains supplementary material available at 10.1186/s13063-025-09024-0.

## Introduction

A large percentage of spontaneous intracerebral hemorrhage (ICH) is caused by cerebral small vessel disease (CSVD) [1, 2], either hypertensive arteriopathy (arteriolosclerosis)—associated with non-lobar—or cerebral amyloid angiopathy (CAA), linked to lobar hemorrhages. There are several imaging markers of CSVD such as cerebral microbleeds (CMBs), cortical superficial siderosis (cSS), lacunes, white matter hyperintensities (WMH), and enlarged perivascular spaces (PVS) which can be identified using MRI. The presence and severity of CMBs and cSS in particular have been associated with an increased risk of first ICH and ICH recurrence in patients with CAA [3–5].

Patients with spontaneous lobar ICH often have varying degrees of underlying CSVD on MRI, and the effects of long-term statin therapy on the burden of CSVD have yet to be defined. There is evidence that statin use is independently associated with the presence and increased number of CMBs, especially in cortical locations [6–8] and that statin treatment can reduce incident covert brain infarcts [9]. Determining the association of statin therapy with accrual of CSVD is important, as the accumulation of microvascular insults potentiates vascular cognitive impairment, functional decline, and gait impairment in older age [10–12]. The presence and burden of CSVD markers, in particular CMBs and cSS, may additionally be useful as a screening tool to stratify the benefit-risk of statin therapy in ICH survivors taking statins and to monitor the effects of statins on the progression of these markers and potentially increased propensity to recurrent ICH. Many physicians take these imaging features into consideration to guide their therapeutic decisions in patients with ICH [13]. However, evidence from randomized controlled trials (RCTs) supporting the prognostic value of these imaging features in ICH patients is lacking.

The SATURN-MRI ancillary study provides a synergistic opportunity to examine the prognostic and pathophysiological characteristics of MRI biomarkers of CSVD within the scope of a large-scale, prospective RCT.

## Methods

### Study design

SATURN-MRI is an ancillary study of the parent StATins Use in intRacerebral hemorrhage patieNts (SATURN) trial which is an international, multi-center, pragmatic, prospective, randomized, open-label, Phase III clinical trial with blinded end-point assessment (PROBE) [14]. Briefly, SATURN aims to evaluate the risks of symptomatic recurrent ICH (i.e., any neurological deficits or clinical symptoms resulting in brain imaging and diagnosis of ICH) and major adverse cardiovascular or cerebrovascular events (MACCE) with continuation vs. discontinuation of statin drugs during a 2-year follow-up period in patients presenting with spontaneous lobar ICH while on a statin [14]. A subset of patients participating in SATURN will be enrolled in SATURN-MRI. Participation in SATURN-MRI is optional.

### Study objectives

#### Primary objective

To determine the effects of continued long-term statin therapy compared to statin discontinuation on the incidence of new hemorrhagic MRI markers (CMBs and cSS) on end-study MRI in patients with lobar ICH. We hypothesize that the proportion of patients with new CMBs and/or cSS on end-study MRI will be higher among those who continue statin therapy.

#### Secondary objectives

To assess whether the presence and burden of CMBs and cSS on baseline MRI modifies the effects of statin on the risk of recurrent symptomatic ICH and can potentially be used as an imaging marker to stratify the benefit-risk of statin therapy in patients with lobar ICH. We also aim to examine the modifying effects of these markers on the risk of MACCE.To evaluate the effects of statin continuation vs. discontinuation on the incidence of new ischemic MRI markers (white matter hyperintensities (WMH) and covert infarcts) on end-study MRI.To evaluate interactions between statin continuation vs. discontinuation, accrual of MRI markers of CSVD, and functional and cognitive outcomes at the end of the study at 24 months.

### Patient population

SATURN-MRI population will be drawn from the participants in the SATURN parent trial [14]. The inclusion/exclusion criteria for the SATURN trial have been previously described [14]. Briefly, patients aged 50 years or older presenting with a spontaneous lobar ICH while taking a statin drug who are randomized into SATURN will be asked to participate in SATURN MRI. Participants in SATURN MRI must meet all of the eligibility criteria for SATURN. In addition, [1] the subject or surrogate must opt in to participate in the MRI study; and [2] the subject must have no known contraindications to MRI such as claustrophobia, metal implants, or pacemaker. Participants will be prospectively enrolled at approximately 140 hospitals in the United States, Canada, and Spain.

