### Randomization

Patients will be randomized into the SATURN trial using the following stratification variables: clinical site, statin dose and indication (primary vs. secondary prevention), current use or intent-to-use oral anticoagulants and/or antiplatelets in the long-term post-ICH, and severity of ICH upon presentation as assessed by baseline ICH volume. There is no additional randomization procedure for the SATURN-MRI ancillary study.

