### Intervention

Participants will undergo a standardized brain MRI protocol during hospitalization within 7 days of randomization into SATURN and again within 30 days of the 24-month end-of-study period. Subjects who already undergo a baseline MRI as part of institutional practice are not required to undergo a repeat baseline study-specific MRI to participate in SATURN-MRI, provided that the MRI complies with the study imaging protocol (Table 1).

**Table 1 Tab1:** SPIRIT figure

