### Statistical considerations

#### Sample size calculations

The target sample size is 894, based on the following observations/assumptions. We previously reported that 57% of statin-treated patients admitted with acute lobar ICH had CMBs on MRI [6]. Although the estimated incidence rate of new CMBs per year in patients with lobar ICH on/off statins is unknown, the annual incidence rate in mixed stroke cohorts varies from 3 to 7% per year (average ~ 5% per year) [18–21]. In a cohort of 118 patients with probable CAA, 8.5% showed new CMBs without cSS progression, 18.6% showed cSS progression without new CMBs, and 9.3% showed new CMBs and cSS progression, for a total of 36.4% with progression of either CMBs and/or cSS over the 2.2 years of follow-up, or approximately 19% per year [18]. These data likely overestimate the incidence rate expected in SATURN-MRI because approximately 33% of SATURN patients are expected to have probable CAA, and another 40% possible CAA. Therefore, we opted to select a more conservative new CMB and/or cSS rate of 6% per year, for a total of 12% over 24 months in patients discontinuing statins. We postulated that statin therapy will increase the risk of new CMB and/or cSS at a rate that is similar to that reported for ICH in the SPARCL trial (HR 1.68, or absolute increase of 8% over 24 months). Based on these assumptions, a two-group comparison of independent proportions with 652 subjects will yield 80% power to detect an absolute increase of 8 percentage points associated with the continuation of statin therapy in SATURN. This sample size was further inflated to account for loss-to-follow-up (LTFU), withdrawal-of-consent, and death during the 2-year follow-up period of approximately 15%, as observed in other MRI sub-studies, such as NAVIGATE-ESUS [22] and PURE [23].

The sample size calculation assumes 1:1 statin continuation:discontinuation among subjects enrolled in the ancillary SATURN-MRI study, but this balance is not guaranteed. However, the power is maintained above 75% for allocation ratios in the interval between 0.6 (discontinuation arm 62.5% of the total sample) and 2.5 (discontinuation arm 28.6% of the total sample).

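### The article asks patients to join the MRI study after open-label randomisation, but Table 1 puts consent before allocation; if the text is followed, MRI entry can depend on the arm

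*Protocol article*

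**What the plan says.** The Study design section describes the parent trial as an "international, multi-center, pragmatic, prospective, randomized, open-label, Phase III clinical trial" in which only end-point assessment is blinded. It adds: "Participation in SATURN-MRI is optional". The Patient population section says that patients "who are randomized into SATURN will be asked to participate in SATURN MRI" and makes it a condition of entry that "the subject or surrogate must opt in to participate in the MRI study". The Randomization section states: "There is no additional randomization procedure for the SATURN-MRI ancillary study". MRI participation is not among the stratification variables listed there.

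The Intervention section describes a "standardized brain MRI protocol during hospitalization within 7 days of randomization into SATURN" and accepts a clinical MRI already obtained if it meets the imaging protocol. Table 1 marks both informed consent and the baseline MRI in the enrolment column, ahead of the allocation column.

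The Sample size calculations section assumes equal arms "among subjects enrolled in the ancillary SATURN-MRI study, but this balance is not guaranteed". It then gives the range of continuation:discontinuation ratios, 0.6 to 2.5, over which power stays above 75%.

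**The concern.** The MRI study borrows the parent trial's randomisation. That works only if the decision to join cannot be influenced by the assigned arm. Opt-in fixed before allocation guarantees this. Opt-in requested afterwards in an open-label trial does not, because the patient, the surrogate and the site can all know the arm when the question is put.

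Willingness to join could then differ by arm in a way linked to underlying vessel disease. The arms of the MRI subset would differ at baseline in what drives the primary outcome, new microbleeds or siderosis. The result could be a false effect or a masked one, and a larger sample would not cure either. The article gives the order in two ways and does not say which applies to MRI opt-in.

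**Working it through.** **1. The passages side by side.**

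| Place | Invitation or consent | Baseline MRI |
|---|---|---|
| Patient population | Put to patients already randomised | – |
| Intervention | – | Within 7 days of randomisation; earlier compliant clinical MRI accepted |
| Table 1 | Enrolment column, before allocation | Enrolment column, before allocation |

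The firm conflict is in the order of invitation and allocation. The scan timing conflicts less clearly, since a window around randomisation can include earlier scans.

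**2. Do the planned safeguards cover selection at entry?**
- Intention-to-treat (Data analyses) can apply only to those who opted in.
- The named covariates are statin dose and indication, antithrombotic use or intent, and severity of the enrolling ICH. Baseline microbleeds, siderosis and CAA status are not among them.
- Blinded reading (Imaging analyses) protects measurement, not entry.
- Multiple imputation (Lost-to-follow-up and missing data) fills in missing outcomes of participants; people who never joined are outside it.

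**3. Reproducing the plan's figures.** Inputs: 12% versus 20%, 80% power. The significance level is not stated; two-sided 0.05 is assumed. Unpooled formula:

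n per arm = (1.960 + 0.842)² × (0.12×0.88 + 0.20×0.80) / 0.08² = 7.849 × 0.2656 / 0.0064 ≈ 325.7, so 326 per arm and **652** in total, as stated.

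Power at N = 652 is Φ(0.08 / √(0.1056/n_disc + 0.16/n_cont) − 1.96):
- ratio 0.6 (407.5 discontinuation, 244.5 continuation): 75.4%
- ratio 1: 80.0%
- ratio 2.5 (186.3 discontinuation, 465.7 continuation): 75.5%

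The stated range is therefore arithmetically right. Its ends are where power falls to about 75%. It concerns group sizes only, not the prognostic mix within them.

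**4. Illustration of what arm-dependent opt-in could do.** From the article: 33% of patients in a high-risk stratum (its expected share with probable CAA), 12% overall risk, N = 652. Assumed: high-risk progression h of 20%, 24% or 30%, the opt-in rates below, and no true effect.

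Low-risk progression is (0.12 − 0.33h)/0.67, giving 8.1%, 6.1% or 3.1%.

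*Scenario A:* opt-in is 60% everywhere except 40% among high-risk continuation patients.
- Continuation opt-in: 0.33×0.4 + 0.67×0.6 = 0.534. Discontinuation opt-in: 0.60.
- Arm ratio: 0.534/0.60 = 0.89. Discontinuation share: 0.60/1.134 = 52.9%.
- High-risk share in continuation: 0.132/0.534 = 24.7%, against 33% in discontinuation.
- For h = 24%, continuation risk is 0.247×0.24 + 0.753×0.061 = 10.5%, against 12.0%: a spurious difference of −1.5 points.

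*Scenario B:* opt-in is 60% high-risk and 50% low-risk in discontinuation (0.533 overall), and 40% and 60% in continuation (0.534 overall). The arm ratio is 1.00.

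| Scenario | h | Spurious difference (points) | Type I error | Power if true risk ratio is 20/12 |
|---|---|---|---|---|
| A | 20% | −1.0 | 6.8% | 62% |
| A | 24% | −1.5 | 9.2% | 51% |
| A | 30% | −2.2 | 15.0% | 35% |
| B | 20% | −1.5 | 9.1% | 54% |
| B | 24% | −2.2 | 14.4% | 40% |
| B | 30% | −3.3 | 26.8% | 21% |

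Type I error is two-sided. Power uses the pooled-variance test, which gives 79.7% when opt-in does not depend on arm; the difference is then 0 and type I error 5%. If the continuation arm instead over-represented high-risk patients, the spurious difference would be positive, the direction of the study hypothesis.

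**The case against.** The article does not state that the arm is known when the patient is asked. That is inferred from the word order in Patient population plus the open-label design. The sentence is part of a brief summary of the population and may compress a single consent process. Table 1, the only schedule shown, already has the safer order, and an article commonly leaves consent details to the full protocol. The consent row in Table 1 is not labelled as parent or MRI consent, and a scan before allocation can fit the Intervention section. All of this stands. It makes the point conditional, and if opt-in is in fact taken before allocation, a clarifying sentence settles it. It does not remove the conflict, because the article's own text gives the other order.

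A reader might go further and infer that the ratio range of 0.6 to 2.5 amounts to planning for selective opt-in, since chance alone at 652 gives only about 0.86 to 1.17 (from 0.5 ± 1.96 × 0.5/√652). The documents do not support this. The section assumes 1:1 and reports where power holds; it forecasts no such ratios. The interval includes the whole chance range. Differential death, withdrawal or dropout could also shift the ratio among the 652 evaluable. The caveat about balance can simply reflect that the subset has no randomisation of its own.

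Nor is the arm ratio a usable alarm: scenario A passes at 0.89, and scenario B at 1.00.

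**Conclusion.** The concern holds in conditional form. The article describes the order of MRI invitation and allocation in two ways that must be reconciled. If the Patient population text is followed as written, entry to the MRI study can depend on the arm, the primary comparison is not fully protected by randomisation, and no planned safeguard restores that protection. The sample size section's allowance for imbalance is correct but answers a different question.

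The documents do not show that bias will occur, and its size and direction cannot be derived from them. The illustration, a false difference of 1.0 to 3.3 points against a target of 8, rests on assumed opt-in rates and stratum risks. It shows only that moderate selection could matter while the arms look balanced in number. The conclusion also assumes that nothing in the full protocol already fixes MRI opt-in before allocation is disclosed.

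**What to change.** - State that SATURN-MRI opt-in (yes or no) is recorded at parent-trial consent, before allocation is released. The scan itself may still follow within 7 days.
- Align the Patient population and Intervention sections with Table 1, and label the consent row in Table 1 as covering MRI opt-in.
- Define the primary analysis set as everyone who opted in before allocation, with missing end-study MRIs handled by the imputation already planned.
- For anyone who opted in after allocation: adjust for baseline microbleeds and siderosis, which the study already collects; compare joiners with non-joiners within each arm on parent-trial baseline data; and show a sensitivity analysis without them. Adjustment deals only with selection through those measured markers, so it supplements the consent order and does not replace it.
- Add a sentence to the sample size section saying that the ratio range concerns power and gives no assurance about bias.

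The cost is a small amendment, the need to ask about MRI at enrolment, and a little extra analysis. The 652 evaluable participants required do not change.

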### Randomization

Patients will be randomized into the SATURN trial using the following stratification variables: clinical site, statin dose and indication (primary vs. secondary prevention), current use or intent-to-use oral anticoagulants and/or antiplatelets in the long-term post-ICH, and severity of ICH upon presentation as assessed by baseline ICH volume. There is no additional randomization procedure for the SATURN-MRI ancillary study.

### Intervention

Participants will undergo a standardized brain MRI protocol during hospitalization within 7 days of randomization into SATURN and again within 30 days of the 24-month end-of-study period. Subjects who already undergo a baseline MRI as part of institutional practice are not required to undergo a repeat baseline study-specific MRI to participate in SATURN-MRI, provided that the MRI complies with the study imaging protocol (Table 1).

**Table 1 Tab1:** SPIRIT figure

	**Study period**							
	Enrolment	Allocation	Post allocation					Close-out
TIMEPOINT	-t	0	T_1_	T_2_	T_3_	T_4_	T_8_	t_x_
ENROLMENT:								
Eligibility – screen	X							
Informed consent	X							
Randomization procedures								
Allocation		X						
INTERVENTIONS:								
Intervention A: Statin		X						
Intervention B: No Statin		X						
ASSESSMENT:								
MRI baseline	X							
MRI follow-up							X	

### MRI protocol

Study sites are required to use a standardized brain MRI protocol to minimize variability from site to site and keep the same field strength and T2*-weighted sequence for the same subject, whenever possible, for both the initial and follow-up MRI to maximize the precision of image analyses and incident lesions. The MRI protocol must include the following: T1-weighted, T2-weighted, fluid attenuated inversion recovery (FLAIR), diffusion-weighted, and T2*-weighted (either a gradient-echo [GRE], susceptibility-weighted [SWI], or T2*-weighted angiography [SWAN]) sequences with parameters consistent with Standards for Reporting Vascular Changes on Neuroimaging (STRIVE) consensus guidelines for imaging manifestations of small vessel disease [15] (Supplementary Table 1). MRI scanners with field strengths ranging from 1.5 to 3.0 T are allowed depending on the site’s capabilities.

### Imaging analyses

Experienced readers, blinded to clinical details including treatment assignment, at the imaging core lab at the Seaman Family MRI Center at the University of Calgary will analyze the images. FDA compliant OsiriX software (Pixmeo SARL, Geneva, Switzerland) will be used to view the images. All incident lesions will be defined according to consensus guidelines for CMBs detection and STRIVE [15]. CMBs will be categorized by number (0, 1–2, 3–10, or > 10) and location (lobar, deep, or mixed deep/lobar), while cSS will be categorized as focal (involving ≤ 3 sulci) or disseminated (if involving ≥ 4 sulci). Covert infarcts will be defined as lesions in a vascular territory that are hyperintense on T2-weighted or FLAIR and hypointense on T1-weighted images, and if subcortical, they need to be at least 3 mm in size and have a round or ovoid shape to distinguish them from a perivascular space. Infarcts will furthermore be classified by size (> 15 or ≤ 15 mm axial diameter) and location (including cortical vs. subcortical and by lobe). Dilated perivascular spaces (Virchow-Robin) will be distinguished from infarcts on the basis of location, morphology, diameter (generally < 3 mm), and the absence of gliosis. Diffusion-weighted (DWI) hyperintense lesions will be defined as remote areas outside of the perihematomal border that are hyperintense on DWI with either corresponding hypointensity or isointensity on acute diffusion coefficient (ADC) sequences. White matter hyperintensities (WMH) will be divided into periventricular or deep and rated visually using the Fazekas scale. Semi-automated quantitative measurement of WMH volume will also be carried out using a Lesion Extraction Tool (University of Calgary; Calgary, AB, Canada).

### Study outcomes

The primary outcome is new CMBs and/or sulci with cSS on T2*-weighted (GRE or SWI) images at end-study compared to baseline. Additional outcomes include the count of new CMBs, progression of WMH, and incidence of covert new non-lacunar infarcts between baseline and end-study MRIs. Clinical outcomes of (i) recurrent ICH, (ii) MACCE, (iii) cognitive decline (telephone T-Montreal Cognitive Assessment T-MoCA; https://mocacognition.com/), and (iv) poor functional outcome (modified Rankin Scale (mRS) 4–6) [16, 17] will also be assessed to determine if their relationship with statin use is modified by the presence and burden of CMBs and cSS on baseline MRI. The details on how functional and cognitive outcomes are assessed and collected are described elsewhere [14].

